### Hypothermic Oxygenated Machine Perfusion Versus Historic Cold Storage Group

Primary and secondary outcomes of patients transplanted with the HOPE-treated kidneys will be compared to a case-matched group of 30 patients (1:2 matching) transplanted with ECD organs after conventional cold storage, using identical surgical techniques and perioperative treatment at the Department of Surgery and Transplantation, University Hospital RWTH Aachen. The present trial comprises two groups, a perfusion (Group 1, HOPE) and a control conventional cold storage group (Group 2, Historic). Patients on the waiting list for kidney transplant with proven written consent will be recruited. HOPE will be applied to the allograft in the operating room after regular organ procurement, transport, and back-table preparation (Figure 1).

We adapted a protocol based on clinical studies with nonoxygenated hypothermic machine perfusion, and on preclinical experience with HOPE [11,18,19]. HOPE will be applied through the renal artery for at least two hours, with a perfusion pressure of 25 mmHg and a perfusion rate of 50-200ml/min using 1 L of recirculated perfusate at 0-4°C. The perfusate will be oxygenated using medical grade oxygen (O^2^), with a partial pressure of oxygen (pO^2^) of 60-80 kilopascals (kPa), by an oxygenator included as a disposable part of the setup. Perfusion parameters registered by the device will be stored automatically and evaluated for possible patterns. Immediately prior to perfusion, grafts will be flushed with perfusate solution to wash out the residual histidine-tryptophan-ketoglutarate (HTK) solution. Storage, management, and use of the medical products will be carried out according to the manufacturer’s guidelines.

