### Sample Collection and Storage

Ischemia reperfusion injury will be assessed using kidney tissue samples taken upon arrival of the organ (before HOPE) and at the end of implantation after reperfusion, but before closure of the abdomen, to evaluate the extent of IRI (Figure 3). In total, two biopsies using BARD MONOPTY Disposable Core Biopsy Instrument (Bard Biopsy Systems Inc, Tempe, Arizona) will be harvested from the ECD kidney allograft and used for translational research. During machine perfusion, perfusate samples will be collected every 20 minutes. Blood samples are taken as part of the daily routine during the perioperative and postoperative course of kidney transplant (Figure 3). Blood parameters of kidney function (ie, creatinine, urea, estimated glomerular filtration rate [eGFR]) will be monitored. An additional 20 mL of blood will be drawn on postoperative days 1, 2, 3 and 7 and will be used for translational research (Figure 3). All kidney tissue, serum, and perfusate will be directly snap-frozen in liquid nitrogen (−80°C) and stored for 6 months after completion of the trial. To assess the subcellular mechanisms of HOPE in the clinical setting, various parameters, including markers of kidney injury (creatinine and neutrophil gelatinase-associated lipocalin (NGAL) in plasma samples), tissue ATP concentration, inflammatory mediators (eg, tumor necrosis factor alpha, interleukin-6, macrophage migration inhibitory factor, interleukin-10, monocyte chemoattractant protein-1), and biomarkers of oxidative damage (eg, 8-hydroxy-2'-deoxyguanosine), will be analyzed [11,12].

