### Immunosuppression and Postoperative Care

All patients will be treated according to our institutional protocol. Aside from HOPE for the donor kidneys, all procedures, including peri- and intraoperative management, are conducted in accordance with standard surgical kidney transplant management. The applied immunosuppressive regimen is based on intraoperative induction therapy with intravenous methylprednisolone and either basiliximab or thymoglobulin followed by corresponding oral doses of prednisolone, tacrolimus, and mycophenolate mofetil.

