### Study Endpoints

The primary endpoint is DGF, which is defined as the need for dialysis in the first 7-days posttransplantation. The secondary endpoints of the study include: (1) duration of DGF (defined as the period between kidney transplant and last dialysis in days) and functional DGF (defined as <10% fall in serum creatinine for 3 consecutive days in the first week posttransplantation); (2) creatinine reduction ratio day 2 ([creatinine day 1−creatinine day 2]/creatinine day 1) and Creatinine reduction ratio day 5 ([pretransplant creatinine−creatinine day 5]/pretransplant creatinine); (3) incidence of postoperative complications, as assessed by the Clavien-Dindo complication score and the comprehensive complication index [22]; (4) duration of intensive care and hospital stay; (5) recipient and graft survival after six months; (6) renal function (assessed by serum creatinine and eGFR) at one-, three- and six-months post-transplant; and (7) basic and translational research, which involves assessing biomarkers from routinely harvested kidney tissue and serum following implantation to obtain information on kidney injury, extent of oxidative damage, redox- and energetic homeostasis of the implanted donor kidney.

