### Study Population

To the best of our knowledge, aside from a sole case of HOPE-treated dual kidney transplant reported recently, no experience of HOPE in human donation after brain death kidney transplant has been published yet [23]. In the present pilot study, 15 patients (N=15) will be treated with HOPE to gain first prospective clinical knowledge. HOPE-treated patients will be compared to a case matched group of 30 patients (N=30).

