### Data Collection and Statistics

Patients will be given consent forms while in our outpatient clinic. Data will be obtained using study specific CRFs completed by the members of the study team. Subjects will be informed about data protection, including pseudonymization. Encoded data will only be provided to authorized persons (ie, authorized study staff, authorities, institutional review board). The study will be prematurely terminated for any individual subject in case of study-related complications or if the subject withdraws informed consent. Parametric and nonparametric tests will be done according to the normality of the data distribution. Two-way analysis of variance will be used for the time-course analysis of laboratory parameters. The log-rank test will be used for comparisons between Kaplan-Meier curves of six-month graft survival. Statistical significance will be defined as *P*<.05.

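### Postoperative complications are compared between prospectively followed HOPE patients and historic controls with no rule for equal capture, and the article does not settle whether controls had the biopsies

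*Protocol article*

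**What the plan says.** **Endpoint.** Study Endpoints lists as its third secondary endpoint the "incidence of postoperative complications, as assessed by the Clavien-Dindo complication score and the comprehensive complication index".

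**Comparison.** The section on HOPE versus the historic cold storage group states: "Primary and secondary outcomes of patients transplanted with the HOPE-treated kidneys will be compared to a case-matched group of 30 patients (1:2 matching". It names the comparator as "a control conventional cold storage group (Group 2, Historic". Study Population says that "15 patients (N=15) will be treated with HOPE to gain first prospective clinical knowledge". Table 1 gives this trial's enrolment as 15, which is the HOPE group alone.

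**Data capture.** The Figure 3 caption lists eight study visits: screening, admission, postoperative days 1, 2, 3 and 7, discharge, and 6 months. Data Collection and Statistics says: "Data will be obtained using study specific CRFs completed by the members of the study team". It does not name a group.

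**Biopsies.** Sample Collection and Storage says: "In total, two biopsies using BARD MONOPTY Disposable Core Biopsy Instrument" will be taken from each graft for translational research. One is timed before HOPE, the other after reperfusion and before the abdomen is closed.

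**Similarity of care.** The historic-group section describes controls as transplanted "using identical surgical techniques and perioperative treatment". Immunosuppression and Postoperative Care adds: "Aside from HOPE for the donor kidneys, all procedures, including peri- and intraoperative management, are conducted in accordance with standard surgical kidney transplant management". The last secondary endpoint describes the kidney tissue as harvested in routine practice, and Safety Considerations says the biopsies follow clinical standards and carry no relevant study-related risk.

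**The concern.** A graded complication endpoint depends on how closely events are looked for and written down, most of all for minor events. Need for dialysis or graft loss depends on this much less. If one group is documented by a study team and the other is reconstructed from existing notes, the comparison mixes any effect of HOPE with a difference in documentation. Matching cannot repair this: donor urine output, cold ischemic time and the Charlson index govern who is compared, not how outcomes are recorded.

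The biopsies raise a second question. If they are a study procedure done only in HOPE patients, any biopsy-related bleeding counts as a complication in that group alone, and the statements that care is identical or standard apart from HOPE need qualifying. If biopsy was routine in controls too, there is no such difference, but the sampling section should say so.

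At stake is the reading of one secondary endpoint: a real reduction in complications could be masked, or an apparent excess produced.

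**Working it through.** The plan gives no complication rate, no capture rate and no power calculation for this endpoint, so it has no figure to reproduce. The check has two parts.

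**1. What follows from the text on capture**

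- The comparator is labelled historic, and enrolment (15) equals the HOPE group. The 30 controls were therefore not seen at the study visits.
- Their complications must come from existing records, even if later copied onto a CRF. This is an inference, but the text leaves little room for another reading.
- The article gives no common source, form or window for grading both groups.

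**2. Illustrative size (all rates assumed)**

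Inputs from the article: 15 HOPE patients, 30 controls, significance at P<.05 (taken as two-sided). Assumptions: no true HOPE effect, the same true proportion *p* with at least one complication in both groups, full capture in HOPE, and capture *s* of affected controls from records.

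Spurious excess in HOPE = p − p·s = p(1 − s).

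- p = 0.60: 0.60 × 0.10, 0.20, 0.30 = 6, 12, 18 points for s = 90, 80, 70%.
- p = 0.40: 0.40 × 0.10, 0.20, 0.30 = 4, 8, 12 points.
- p = 0.80: 0.80 × 0.10, 0.20, 0.30 = 8, 16, 24 points.

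The chance of an uncorrected chi-squared P<.05, summed exactly over all outcomes of 15 versus 30:

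| True rate | s = 100% | s = 90% | s = 80% | s = 70% |
|---|---|---|---|---|
| 40% | 4.8% | 5.9% | 8.9% | 13.9% |
| 60% | 4.8% | 6.1% | 10.9% | 19.6% |
| 80% | 5.0% | 8.8% | 19.5% | 35.6% |

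Masking of a real effect: if HOPE truly lowered the rate from 60% to 42%, controls captured at 70% would show 0.60 × 0.70 = 42%, an observed difference of zero.

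Biopsy: one event in a HOPE patient otherwise free of complications adds 1/15 = 6.7 points. The documents give no biopsy event rate. If biopsy caused a complication in an assumed 5% of patients otherwise free of one, then at p = 0.60 the HOPE rate becomes 0.60 + 0.40 × 0.05 = 62%, and the excesses become 62 − 54 = 8, 62 − 48 = 14 and 62 − 42 = 20 points.

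These figures concern the proportion with any complication. They do not carry over directly to the comprehensive complication index.

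**The case against.** The case on the other side has several sound parts.

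- **Disclosed limitation.** The Discussion concedes non-randomisation, a non-blinded transplant team and historical matching, and presents the trial as a pilot. That covers the general weakness. It neither names nor repairs unequal outcome capture.
- **Control abstraction is not described.** The CRF sentence names no group, and donor data are also transferred to CRFs, so a CRF alone does not prove a separate prospective source. An article may leave abstraction detail to the full protocol. This stands, and the point does not rest on the missing detail. It rests on the stated comparison of enrolled patients with a historic group.
- **Surveillance may differ little.** Six of the eight visits fall between admission and discharge, when every patient is under institutional care. The caption shows only one later visit. This stands and limits the likely size.
- **The magnitudes are assumed.** A control drops out of the any-complication count only if all of that patient's events were missed, so 70% capture is an unfavourable assumption. This stands too.

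A reader might also infer more than the documents support:

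- **That only HOPE patients were biopsied.** No section says controls were not. The research purpose and the timing relative to HOPE suggest a study procedure, while the references to routine tissue and clinical standards leave routine biopsy open.
- **That the sections flatly contradict each other.** The statements concern surgical technique, perioperative treatment and standard management, and a tissue sample is arguably none of these. The text is unsettled rather than provably wrong.
- **That the bias must run against HOPE.** Unblinded graders could favour HOPE.
- **That the trial's safety decision is affected.** The stated stopping rule uses the delayed graft function rate, not this endpoint.

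**Conclusion.** The point holds as a modest, inexpensive improvement. As described, the complication comparison sets prospectively followed patients against a group whose events can only be read from existing records. That would tend to under-count minor events in controls. Net direction is not certain and the size is unknown. At an assumed 60% true rate with 10% to 30% of affected controls missed, the spurious excess in HOPE is 6 to 18 points; over assumed true rates of 40% to 80% it is 4 to 24 points. These figures rest wholly on the assumed rates and on full capture in HOPE.

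On the biopsies, the conclusion is narrower: the article does not settle whether they are a study-only procedure or were routine in controls. Unequal capture is the stronger half of the point.

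**What to change.** 1. For the between-group comparison, score Clavien-Dindo and the comprehensive complication index in both groups from the same routine records, on the same abstraction form and over the same window from transplant. Keep events found only on the CRF as a descriptive safety listing for HOPE.
2. Flag biopsy-attributable events and report the endpoint with and without them.
3. Reconcile Sample Collection and Storage with Study Endpoints, the historic-group section, and Immunosuppression and Postoperative Care: state whether biopsy is a study procedure or was routine in controls.
4. Optionally, add a comparison restricted to grade III or higher as a sensitivity analysis. It should not replace the main comparison, since it leaves fewer events in groups of 15 and 30.

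Cost: wording changes and extra chart abstraction for the 15 HOPE patients. Events recorded only on CRFs drop out of the comparison. Capture will still not be perfectly equal, because notes on HOPE patients are written during a known, unblinded study.

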### Study Population

To the best of our knowledge, aside from a sole case of HOPE-treated dual kidney transplant reported recently, no experience of HOPE in human donation after brain death kidney transplant has been published yet [23]. In the present pilot study, 15 patients (N=15) will be treated with HOPE to gain first prospective clinical knowledge. HOPE-treated patients will be compared to a case matched group of 30 patients (N=30).

### Data Collection and Statistics

Patients will be given consent forms while in our outpatient clinic. Data will be obtained using study specific CRFs completed by the members of the study team. Subjects will be informed about data protection, including pseudonymization. Encoded data will only be provided to authorized persons (ie, authorized study staff, authorities, institutional review board). The study will be prematurely terminated for any individual subject in case of study-related complications or if the subject withdraws informed consent. Parametric and nonparametric tests will be done according to the normality of the data distribution. Two-way analysis of variance will be used for the time-course analysis of laboratory parameters. The log-rank test will be used for comparisons between Kaplan-Meier curves of six-month graft survival. Statistical significance will be defined as *P*<.05.

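### Two-way ANOVA is named for serial laboratory values with no provision for within-patient correlation; run with group and time factors only, its group test would not hold the 5% level

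*Protocol article*

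**What the plan says.** Under Data Collection and Statistics, the protocol article fixes the method: "Two-way analysis of variance will be used for the time-course analysis of laboratory parameters". The same section sets one threshold for all tests ("Statistical significance will be defined as" P<.05).

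Three other sections show that the values are serial within patients:

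- Sample Collection and Storage: "Blood parameters of kidney function (ie, creatinine, urea, estimated glomerular filtration rate [eGFR]) will be monitored", and "Blood samples are taken as part of the daily routine during the perioperative and postoperative course of kidney transplant". It adds "An additional 20 mL of blood will be drawn on postoperative days 1, 2, 3 and 7"; these extra draws are for translational research.
- Study Endpoints lists, as a secondary endpoint, "renal function (assessed by serum creatinine and eGFR) at one-, three- and six-months post-transplant".
- Study Population gives the group sizes: "15 patients (N=15) will be treated with HOPE to gain first prospective clinical knowledge", and "HOPE-treated patients will be compared to a case matched group of 30 patients (N=30").

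The article does not say how correlation between values from one patient is handled. It gives no estimate of that correlation and does not say which occasions enter the analysis.

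**The concern.** A comparison of two groups over time by two-way ANOVA has group and time as its factors. Without a patient term, every value counts as an independent observation: four values from each of 45 patients become 180 observations with 172 error degrees of freedom, although only 45 patients inform the group contrast.

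With positive within-patient correlation this has two opposite effects. The group effect is judged against too small an error, so chance differences between the 15 and the 30 patients are declared significant too often. The group-by-time effect is judged against too large an error, so a real difference in the shape of recovery is harder to detect. In a small pilot with a short-term focus, the serial kidney-function values could then be misread in either direction.

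**Working it through.** **Inputs from the article.** Groups of 15 and 30; nominal level 0.05; possible occasions on days 1, 2, 3 and 7 (T = 4) and months 1, 3 and 6 (T = 3), or T = 7 if both sets are joined.

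**Assumed.** The within-patient correlation ρ is varied from 0 to 0.9, under compound symmetry and under AR(1) with equally spaced occasions. Data are complete and normal, there is no true group effect, and the matching is ignored. The article has no error-rate or power figure for this analysis, so the only figure to check is the nominal 5%.

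**Group test without a patient term, analytic.** Under compound symmetry the variance of a patient mean over T values is inflated by the design effect

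DE = 1 + (T − 1)ρ,

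and the actual two-sided level is about

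α* = 2[1 − Φ(1.96/√DE)].

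- T = 4, ρ = 0.1: DE = 1.3; 1.96/1.140 = 1.719; α* = 0.086
- T = 4, ρ = 0.3: DE = 1.9; 1.96/1.378 = 1.422; α* = 0.155
- T = 4, ρ = 0.7: DE = 3.1; 1.96/1.761 = 1.113; α* = 0.266
- T = 7, ρ = 0.3: DE = 2.8; 1.96/1.673 = 1.171; α* = 0.241
- T = 7, ρ = 0.7: DE = 5.2; 1.96/2.280 = 0.860; α* = 0.390

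**Simulation check.** 10,000 trials per setting; model with group, time and group × time; 43T error degrees of freedom. Rejection rates of the group test under compound symmetry:

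| T | ρ = 0 | 0.1 | 0.3 | 0.5 | 0.7 |
|---|---|---|---|---|---|
| 3 | 0.048 | 0.073 | 0.123 | 0.168 | 0.210 |
| 4 | 0.052 | 0.088 | 0.154 | 0.217 | 0.269 |
| 7 | 0.049 | 0.122 | 0.244 | 0.330 | 0.394 |

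The nominal level holds only at ρ = 0. Under AR(1) the rates are 0.173 (ρ = 0.5) and 0.237 (ρ = 0.7) at T = 4, and 0.212 and 0.310 at T = 7. Decaying correlation reduces the inflation but does not remove it.

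**Group × time test without a patient term.** Under compound symmetry the interaction contrasts vary with (1 − ρ)σ², while the error mean square estimates σ², so the F ratio is scaled by about 1 − ρ. Simulated rejection at T = 4 is 0.031 at ρ = 0.1, 0.010 at 0.3, 0.003 at 0.5 and 0.000 at 0.7. Under AR(1) it is milder in places, for example 0.024 at T = 7, ρ = 0.5.

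**Repeated-measures reading.** With the group effect tested against between-patient error (1 and 43 degrees of freedom), rejection is 4.7-5.1% in every setting under both structures. The uncorrected group × time test is 4.6-5.1% under compound symmetry. Under AR(1) with ρ = 0.5-0.9 it is 5.4-5.8% at T = 3, 5.4-6.7% at T = 4 and 6.5-9.9% at T = 7.

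**The case against.** The strongest reply is that two-way ANOVA for a group-by-time course is often shorthand for the repeated-measures form, and that a condensed article may leave the error term to a fuller document that is not shown. This stands in part. A reader might infer that the plan treats serial samples as independent, but the article never says so. On the repeated-measures reading the group test is sound. What remains is the uncorrected interaction test and the loss of patients with an incomplete series, which matters where graft loss and death within six months are themselves outcomes.

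Three further limits also stand.

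- **Size.** It rests on a correlation that the article does not give. At 0.1 with three or four time points the level is 7-9%, well short of several times nominal.
- **Time grid.** Days 1, 2, 3 and 7 are the schedule of the research draws, and nothing says that the historical controls have them. Months 1, 3 and 6 form a separate endpoint, and nothing says that they join the early values in one model. The seven-point figures, which apply a constant correlation from the first days to month 6, are therefore an upper scenario.
- **Scope.** The day-2 and day-5 creatinine reduction ratios are single values per patient and are not affected. Delayed graft function, its interim rule and graft survival do not use this method.

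The objection does not dispose of the point. The article does not leave the method open: it names one which, followed literally, has no place for the patient.

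**Conclusion.** The point holds conditionally. As written, with group and time the only factors, the group test would run at about 15-27% instead of 5% with four time points and correlations of 0.3-0.7 under compound symmetry. It would run at about 9% at 0.1, and at about 24-39% if seven points were modelled together. The group × time test would be far too conservative, at about 1% or less for correlations of 0.3 and above under compound symmetry. If the repeated-measures form was meant, the group test is valid and the remaining defects are smaller: an uncorrected interaction test at 5-10% under AR(1), and the exclusion of incomplete patients.

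A reader might conclude that a significant HOPE effect on laboratory values would probably be a chance finding. The figures do not support that: the highest rate for correlations up to 0.7 is 39%, and only the group main effect is inflated. The issue is confined to secondary laboratory analyses and does not touch the primary endpoint.

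**What to change.** Replace the ANOVA sentence with a linear mixed model: group, time and group × time as fixed effects, within-patient correlation modelled, and small-sample degrees of freedom. State which occasions enter the model, and report group differences with 95% confidence intervals at prespecified times.

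Keep the covariance parsimonious: a random patient intercept or an AR(1)-type structure. An unstructured matrix has 7 × 8/2 = 28 parameters at seven time points, which is fragile with 45 patients. A random intercept alone implies compound symmetry, so its group × time test would share the 5-10% exposure shown above if correlation decays; an AR(1)-type term deals with that. Log transformation and adjustment for the pre-transplant value are optional.

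Patients with incomplete series then contribute the values they have, on the usual missing-at-random assumption. If the authors prefer repeated-measures ANOVA, the text should say so and add a sphericity correction, accepting the loss of incomplete patients.

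The cost is wording and slightly more analysis work; no visit, sample or patient changes. Intervals for the group effect will be wider, because the literal ANOVA understates them. At T = 4 and ρ = 0.5, for example, the standard error of the group effect averaged over time rises by a factor of √2.5 ≈ 1.58.
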